#### Gut microbiome analysis

The subjects will be instructed to collect faecal samples within 24 h before visits in weeks 0 and 12 and freeze them until the visit. A stool-collecting kit and instructions will be provided to collect the faecal samples, which will be stored at − 80 °C for further analysis. The microbiome community will be evaluated by 16S rRNA sequencing analysis. The relative abundance of the bacterial taxa in each sample will be obtained, and significant differences in the bacterial taxa between the DST group and the placebo group will be evaluated.

### Outcome measures

Because this is a pilot trial, the recruitment rate and completion rate will be calculated to determine feasibility of the study design. The primary outcome of this study will be the mean change in body weight from baseline to the end of the 12-week intervention. Secondary outcomes will include body composition and anthropometric measurements. A transient elastography and physical symptoms questionnaire will be completed at every monthly visit.

### Monitoring

The Korea Institute of Oriental Medicine will be responsible for quality control throughout the study. An independent clinical research associate will regularly monitor the overall process to determine if the trial is being performed in accordance with the protocol, standard operating procedures and the guidelines for good clinical practice. Monitoring will ensure that the investigators have been trained properly and that written consent has been obtained using the appropriate procedures. Monitoring will also include source data verification and a check for maintenance and completeness of essential documents and the eCRF.

### Data collection and management

All source documents, including informed consent forms, questionnaires and worksheets, will be collected in compliance with standard operating procedures. The data will be collected via an electronic data capture system through eCRFs using the Medidata RAVE data management system (Medidata Solutions Inc., New York, NY, USA). The principal investigator will ensure anonymization of the subjects and the confidentiality of all information collected during the course of the trial. The final dataset of the clinical trial will be accessible to all authors. The principal investigator will coordinate dissemination of data. The results will be submitted for publication in peer-reviewed journals.

### Statistical analysis

The statistical analysis will be conducted by an independent statistician using SAS version 9.4 software. The significance level will be set to 5% in a two-tailed test. The multiple imputation method will be adopted for missing data. The intention-to-treat (ITT) principle will be applied for the primary analysis. The ITT principle will include subjects who meet the full analysis set criteria, including subjects who had the primary outcome assessed once or more except for the baseline measures and who took the test drug at least once. The per-protocol set will be analysed in a supplementary analysis, which will only include subjects who have completed the study as the supplementary analysis.

The independent *t* test or Wilcoxon rank-sum test will be used for continuous variables, and the chi-square test or Fisher’s exact test will be used for categorical variables. Analysis of covariance will be performed for the primary outcome and the continuous data of the secondary outcomes. The model will include baseline values and gender as covariates and treatment as a fixed effect. Student’s *t* test or Wilcoxon’s signed-rank test will be used to compare data before and after the treatment within each group. Categorical data will be analysed using the chi-square test or Fisher’s exact test. Additionally, repeated measures analysis of variance will be used to compare differences in trends per visit.

The incidence of SAEs and AEs related to the treatment will be analysed. The percentage of subjects who experience one or more side effects during the study will be analysed and presented using a descriptive analysis for each group.

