### Participants

#### Inclusion criteria

Adults over 19 years to under 65 years of ageObese subjects with body mass index ≥ 25 kg/m^2^Subjects with non-alcoholic fatty liver findings on transient elastography: controlled attenuation parameter (CAP) score > 268 dB/mThose who have voluntarily signed a written consent form approved by the IRB after sufficient explanation of this study

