
### Sample size

This study is a pilot clinical trial to explore the feasibility of DST in obese subjects with NAFLD. No clinical trial has evaluated the efficacy of DST for weight loss and/or NAFLD. Therefore, we calculated sample size based on an opinion from an expert in medical statistics and clinical trials similar to this study that had used herbal supplements for weight loss [18, 19]. According to the previous studies, we assumed the mean and standard deviation of body weight would be 2.2 kg and 2.7, respectively. Thus, the sample size was 30 subjects in each group with a significance level of 5%, power of 80% and drop-out rate of 20%. A total of 60 subjects will be recruited and divided into two groups of 30 subjects each.

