### Randomisation and allocation concealment

Subjects will be randomly allocated to either the DST or placebo group in a 1:1 allocation ratio. Among the various factors affecting the development of obesity and NAFLD, gender differences are the most important factor [20–22]. Because gender differences in NAFLD may have a different impact on the progression of complications, such as non-alcoholic steatohepatitis (NASH), liver fibrosis and hepatocellular carcinoma, subjects were stratified according to gender [23]. The gender distribution for each group will be controlled by an independent statistician using the stratified block randomisation method. The statistician will use SAS version 9.4 software (SAS Institute, Cary, NC, USA) to generate a random allocation list and will send the list to the pharmaceutical company for packing. The allocation for each subject will be sealed in an opaque envelope and will not be disclosed until the clinical trial is completely over, unless serious adverse events (SAEs) happen.

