### Lifestyle guidelines

The subjects will be told to maintain their usual exercise routine and not to change the amount of exercise or kind of exercise they engage in. The Korean version of the International Physical Activity Questionnaire Short Form will be administered to evaluate physical activity status [24]. Daily intake of a low-calorie 20–25-kcal/kg diet will be recommended to increase the weight loss effect. Food intake status will be investigated using 3-day dietary recall before and after the drug intervention. Can-Pro version 5.0 (a computer-aided nutritional analysis program for professionals; Korean Nutrition Society, Seoul, Korea) will be used for the dietary data analysis. Can-Pro is commonly used in Korea to assess nutrient intake because it has a database that reflects the Korean diet.

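### Before-after significance tests within each arm cannot isolate the effect of DST and are not marked descriptive; the planned between-arm ANCOVA is unaffected

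*Protocol article*

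**What the plan says.** The Statistical analysis section sets one general level: "The significance level will be set to 5% in a two-tailed test". It then plans between-arm tests (independent t or rank-sum) and an ANCOVA for the primary outcome and the continuous secondary outcomes, with treatment, baseline value and gender in the model. After that it adds the within-arm tests: a t test or a "signed-rank test will be used to compare data before and after the treatment within each group". Nothing says that these are descriptive or how they will be read.

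Three other places bear on the meaning of a before-after change:

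- Lifestyle guidelines: a low-calorie "diet will be recommended to increase the weight loss effect". The section makes no distinction by arm. The exclusion criteria keep out people already dieting for weight control, so the advice is new to those enrolled.
- Inclusion criteria: entry requires "non-alcoholic fatty liver findings on transient elastography: controlled attenuation parameter (CAP) score" above 268 dB/m, and elastography is later an outcome.
- Study design and Outcome measures: a separate baseline assessment follows within two weeks of qualifying, and elastography is done at each monthly visit. The schedule figure is not available here, and the text does not say which scan is the before value for CAP.

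**The concern.** A before-after test in one arm asks whether that arm changed. It does not ask whether DST changed it more than placebo did. In this design a change is expected for reasons shared by both arms: new diet advice, being observed in a trial and, for CAP, possibly selection on a high reading. The DST arm's change includes any DST effect, but the test cannot separate it from the rest.

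The risk is the familiar reading in which one arm is significant, the other is not, and the pair is reported as evidence of efficacy. With arms this small, that pattern arises often by chance when the arms do not differ. The wording leaves room for it, because the secondary objective speaks of the efficacy of DST on metabolic measures and names no comparator. The tests would also be repeated over many secondary outcomes.

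**Working it through.** **Inputs from the article.** Sample size section: "we assumed the mean and standard deviation of body weight would be 2.2 kg and 2.7, respectively"; 5% level, 80% power, 20% drop-out; 30 per arm. The text says only body weight. I read 2.2 kg as the between-arm difference in weight change and 2.7 kg as the SD of that change.

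**The plan's own figure.** n per arm = 2 × (1.960 + 0.842)² × 2.7² / 2.2² = 23.6, rounded up to 24; 24 / 0.8 = 30. The stated 30 per arm is reproduced, which supports this reading of the SD. I therefore use 24 (completers) and 30 (all recruited).

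**How small a loss is significant within one arm.** Critical mean change = t(0.975, n−1) × 2.7/√n.
- n = 24: 2.069 × 0.551 = 1.14 kg
- n = 30: 2.045 × 0.493 = 1.01 kg

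**Chance findings with no drug effect.** Let both arms have the same true mean loss d. The article gives no placebo-arm loss, so d is assumed and shown over a range. The probability p that one arm shows a significant loss comes from the noncentral t distribution with noncentrality d/(2.7/√n). The arms are independent, so both are significant with probability p², and DST alone with p(1−p).

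Example, d = 1 kg, n = 24: noncentrality 1/0.551 = 1.81; p = 0.412; both 0.412² = 0.170; DST alone 0.412 × 0.588 = 0.242.

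| Shared loss | n per arm | One given arm | Both arms | DST alone |
|---|---|---|---|---|
| 0.5 kg | 24 / 30 | 14% / 16% | 2% / 3% | 12% / 14% |
| 1.0 kg | 24 / 30 | 41% / 50% | 17% / 25% | 24% / 25% |
| 1.5 kg | 24 / 30 | 74% / 84% | 55% / 70% | 19% / 14% |
| 2.0 kg | 24 / 30 | 94% / 98% | 87% / 95% | 6% / 2% |

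A valid two-sided 5% between-arm test wrongly favours DST in 2.5% of trials. At a shared loss of 1 kg, significance in the DST arm alone is about ten times as frequent (25/2.5). At 1.5 kg it is roughly five to eight times as frequent (13.7/2.5 and 19.2/2.5).

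**CAP.** If the qualifying scan is the before value, the expected fall with no change in liver fat is (1 − reliability) × SD × φ(a)/(1 − Φ(a)), with a = (268 − mean)/SD. The article gives none of these inputs. Example: source-population mean 270, SD 50, reliability 0.8 gives a = −0.04 and 0.2 × 50 × 0.773 = 7.7 dB/m. Over means of 250-290, SD 50 and reliability 0.6-0.9, the fall is 2.7-20.8 dB/m. In simulation that alone is significant in one arm in 8-66% of trials (n = 24) or 9-77% (n = 30). With means of 260-300, SD 40-50 and reliability 0.7-0.9, the fall is 1.5-13.5 dB/m. These ranges show how far the answer depends on the assumptions. If a fresh week-0 scan is the before value, the artefact largely disappears.

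**The case against.** The strongest reply is that inference about the drug is already between arms. The same section plans an ANCOVA for the primary and continuous secondary outcomes. Diet advice and selection on CAP act equally on randomised arms, so neither biases that comparison. Nowhere does the article say that a within-arm p-value will be read as a DST effect. This is also an exploratory pilot, and a label such as descriptive could sit in an analysis plan that is not shown. Finally, the shared weight loss and every CAP input are assumed; the diet is only recommended, and subjects are told to keep their exercise unchanged.

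Most of this stands, and it limits the point to supplementary tests. It does not remove it. The article itself commits to these tests under the general 5% level, so the point concerns something stated, not something left out. The planned ANCOVA also shows that the within-arm tests are not needed to judge DST.

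A reader might infer that the within-arm tests will show effects in both arms. The figures do not support that: at a 1 kg shared loss both arms are significant in only 17-25% of trials, and joint significance passes one half only from about 1.5 kg. The two patterns also pull apart. Where both arms are almost always significant (2 kg), DST alone is significant in only 2-6% of trials, and a significant placebo arm would itself restrain a claim.

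**Conclusion.** The point holds as a minor one. The within-arm tests cannot separate DST from influences common to both arms, and nothing marks them as descriptive. If they were read as evidence of efficacy, the false-positive rate in favour of DST would be about 24-25% at a shared loss of 1 kg and 14-19% at 1.5 kg, instead of 2.5%. These figures rest on 2.7 kg being the SD of weight change, on 24 to 30 subjects per arm, and on an assumed shared loss.

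Two wider conclusions are tempting but unsupported. First, the selection on CAP does not by itself cause regression to the mean in body weight, so it has no bearing on the weight comparison. Even for CAP the artefact is conditional: the article describes a separate baseline visit and leaves open which scan is used. Second, nothing here shows an error in the primary analysis or the sample size.

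**What to change.** In the Statistical analysis section, replace the sentence on within-arm tests with two statements: each arm's mean change will be reported with its 95% CI as description, and conclusions about DST will rest on the between-arm ANCOVA difference. If a week-0 CAP scan is taken, name it, and not the qualifying screening scan, as the baseline for describing change in CAP.

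The cost is a sentence or two of text and fewer p-values to report. Sample size, visits and the primary analysis stay as they are.

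### The additional repeated-measures ANOVA of visit trends suits incomplete serial data poorly and should become a mixed model, and the week-12 ANCOVA should be declared the single primary test because the t/Wilcoxon sentence overlaps it

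*Protocol article*

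**What the plan says.** All of the relevant text is in the protocol article. Under Outcome measures, the primary outcome is the change in body weight over the 12-week treatment period. Under Anthropometric measurements, weight is taken at screening and at each monthly visit.

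The Statistical analysis section then gives three between-group methods that could apply to a continuous outcome:

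- A general rule that the independent t test or "Wilcoxon rank-sum test will be used for continuous variables". It is not limited to baseline or secondary data, and no rule is given for choosing between the two tests.
- "Analysis of covariance will be performed for the primary outcome and the continuous data of the secondary outcomes". The model terms are given as baseline value, gender and treatment.
- "Additionally, repeated measures analysis of variance will be used to compare differences in trends per visit". No outcome is named, and nothing is said about sphericity or a correction for it.

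The same section sets one error level for everything ("The significance level will be set to 5% in a two-tailed test") and adopts multiple imputation for missing data. Its full analysis set admits anyone with at least one dose and at least one post-baseline measurement of the primary outcome. The term primary analysis appears there only in connection with the analysis set; no sentence ranks the tests.

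**The concern.** There are two separate issues.

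**The per-visit analysis.** Classical repeated-measures ANOVA works on complete visit vectors, and its univariate within-subject F-test assumes that all differences between pairs of visits have the same variance. The analysis set admits subjects with a single post-baseline weight, and the sample size allows for 20% drop-out, so incomplete vectors are to be expected. The method must then either be restricted to complete cases or be run on imputed data. After imputation, the single treatment coefficient of an ANCOVA combines by Rubin's rules, but a multi-degree-of-freedom F ratio built from sums of squares has no such simple combination. Weight also tends to drift, so visits further apart usually differ more, which is the pattern that sphericity excludes. If the test is left uncorrected, the group-by-visit p-value can be too small.

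**The overlap of tests.** Change in weight is a continuous variable. Read literally, it receives a t or Wilcoxon test as well as the ANCOVA, each at 5%. If the results disagree, the text does not say in words which one counts.

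**Working it through.** **1. The plan's own sample size.** The inputs, from Sample size, are two-sided 5%, power 80% and 20% drop-out, with "we assumed the mean and standard deviation of body weight would be 2.2 kg and 2.7, respectively". The 2.2 kg is read here as a between-group difference in change, which the text does not say.

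n per arm = 2 × (1.960 + 0.842)² × (2.7/2.2)² = 2 × 7.85 × 1.506 = 23.6, rounded up to 24; 24/0.8 = 30.

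The stated 30 per group reproduces. Its basis is an unadjusted two-sample comparison at one time point, so nothing about the repeated-measures analysis enters it.

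**2. What a complete-case run would cost.** This arises only if imputed data were not used. Start from 24 per arm with a week-12 weight, and assume a probability p of missing each of weeks 4 and 8 (p is not in the documents). Complete vectors per arm = 24 × (1 − p)². Power is for a two-sample comparison of 2.2 kg (normal approximation), to show scale.

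| p | Complete per arm | Power |
|---|---|---|
| 0 | 24 | 0.81 |
| 2% | 23.0 | 0.79 |
| 5% | 21.7 | 0.76 |
| 10% | 19.4 | 0.72 |

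With the imputation that the plan adopts, this loss does not occur; the difficulty is then the pooling of the F-tests.

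**3. Type I error, main simulation.** 20,000 null trials were run per setting, with 24 per arm and weeks 0, 4, 8 and 12. The SD of the 12-week change was 2.7 kg. Assumed: baseline SD 12 kg and no gender effect. The Monte Carlo standard error at 5% is √(0.05 × 0.95/20,000) = 0.15 percentage points.

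The two settings differ in the covariance of the changes:

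- *Growing variance* (random walk): the variance of a difference between visits is proportional to the time between them, 2.7² × 1/3, 2/3 or 1, that is 2.43, 4.86 or 7.29 kg².
- *Constant variance, correlation 0.5 between changes*: the variance of any change from baseline is 2.7² = 7.29, and the variance between any two later visits is 7.29 + 7.29 − 2 × 0.5 × 7.29 = 7.29. All differences have equal variance, so sphericity holds; the average estimated epsilon falls slightly below 1.

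| Test at nominal 5% | Growing variance | Sphericity holds |
|---|---|---|
| Average estimated epsilon | 0.63 | 0.94 |
| ANCOVA at week 12 | 5.2% | 4.9% |
| Group-by-visit F, uncorrected | 7.3% | 4.8% |
| Group-by-visit F, Greenhouse–Geisser | 5.1% | 4.4% |
| Any of t, Wilcoxon, ANCOVA | 6.7% | 6.5% |
| Any of those or the uncorrected F | 8.7% | 9.3% |

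**4. Second simulation.** 6,000 null trials were run per setting, with 24 or 30 per arm and linear-slope or random-walk paths, all of which violate sphericity (estimated epsilon about 0.5–0.6). Results: uncorrected F 7.4–8.1%, about 5% with Greenhouse–Geisser; any of t, Wilcoxon or ANCOVA 6.3–6.7%; any of the four 8.6–8.8%. The two sets agree.

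**The case against.** The case against is substantial and removes the stronger readings that a reader might infer.

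- *That subjects with a missed visit are lost.* The documents do not support this. Multiple imputation is adopted in the same section, so subjects drop out only if this analysis were run on unimputed data, which is nowhere stated.
- *That the group-by-visit test is anti-conservative.* It can be, but only if the covariance departs from sphericity and no correction is applied. The text does not say that it will be uncorrected, and a correction is the kind of detail that an analysis plan may hold.
- *That the trial has no primary test.* ANCOVA is the only between-group method assigned by name to the primary outcome, with its terms listed. The t/Wilcoxon sentence is paired with chi-square/Fisher for categorical variables, which are assigned again later in the paragraph. That repetition suggests that the first sentence may be meant for baseline comparisons, although it does not say so.
- *That the real error rate is 8.6–9.3%.* This needs success to be claimable on any of four tests. The plan states no such rule, and the repeated-measures analysis is introduced as additional and names no outcome, so applying it to weight is itself an inference. Even the 6.5% figure supposes that both t and Wilcoxon are run, where the text offers one or the other.

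It may also be said that a mixed model is a matter of taste for a supplementary analysis in a pilot. That part does not fully stand: the article fixes the method by name, incomplete vectors are expected under its own assumptions, and the alternative avoids both the pooling problem and the sphericity assumption. The unrestricted t/Wilcoxon sentence and the absence of any ranking also stand.

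**Conclusion.** The point holds as a modest correction. Repeated-measures ANOVA is a poor choice for serial data with expected gaps. Its group-by-visit test would run at about 7–8% instead of 5% if variance grows over visits and nothing corrects for it, and at about 5% otherwise. These rates rest on assumed covariance patterns, a baseline SD of 12 kg and no gender effect, none of which is in the documents.

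ANCOVA is the natural reading of the primary test and holds about 5% by itself. The overlap with the t/Wilcoxon sentence matters only if a result could be claimed from whichever test succeeds, in which case the rate is about 6.5%. The plan does not authorise that, but it does not exclude it in words either. Neither issue alters the week-12 ANCOVA estimate or the sample size.

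**What to change.** In Statistical analysis:

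1. State that the ANCOVA of week-12 weight change, with treatment, baseline weight and gender, is the single primary test, reported as an adjusted difference with its 95% CI.
2. Limit the t and Wilcoxon tests to baseline comparisons, or label them as sensitivity analyses.
3. Replace the repeated-measures ANOVA with a mixed model for repeated measures: treatment, visit, treatment-by-visit, baseline value and gender, with unstructured covariance. Name the outcomes that it covers and label it supportive. It uses all observed visits, needs no sphericity and avoids pooling F-tests over imputations. With weeks 4, 8 and 12 as responses, the unstructured matrix has 3 × 4/2 = 6 parameters, which is few for a trial of 60.

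The cost is analysis wording only. The SAS version already named can fit the model, no data collection changes, and 30 per group stands.
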